# Impact of a pharmacist-led medication review on hospital readmission in a pediatric and elderly population: study protocol for a randomized open-label controlled trial

**DOI:** 10.1186/s13063-017-1798-6

**Published:** 2017-02-09

**Keywords:** Medication review, Medication reconciliation, Randomized controlled trial, Clinical pharmacy, Pharmacists, Pediatrics, Geriatrics

## Abstract

**Background:**

Early hospital readmission of patients after discharge is a public health problem. One major cause of hospital readmission is dysfunctions in integrated pathways between community and hospital care that can cause adverse drug events. Furthermore, the French ENEIS 2 study showed that 1.3% of hospital stays originated from serious adverse drug events in 2009. Pharmacy-led medication reviews at hospital transitions are an effective means of decreasing medication discrepancies when conducted at admission or discharge. However, it is difficult to assess the true impact of pharmacist-led medication reviews in specific high-risk populations, such as pediatric and geriatric populations.

In such a context, it is important to demonstrate the effectiveness of medication reconciliation as part of a standardized medication review process—in pediatric and elderly populations—on all-cause readmissions in a large randomized controlled clinical trial.

The aim of this study is to assess the impact of the pharmacist-led medication review on the rate of readmissions and/or death after hospital discharge and patient treatment satisfaction.

**Methods/design:**

The study is a randomized controlled clinical trial. A total of 1400 hospitalized patients will be randomized in two groups: (1) the experimental group (group receiving a pharmacist-led medication review) and (2) the control group (group receiving usual care). The pharmacist-led medication review process includes medication reconciliation, treatment review and medication liaison service. The primary endpoint will be the rate of readmissions and/or death at 30 days following initial hospitalization discharge. The secondary endpoints will be the rate of hospital readmission, the rate of emergency department visits, the rate of mortality, the number of consultations and patient treatment satisfaction at 30 days following initial hospitalization discharge.

**Discussion:**

A randomized controlled trial provides the most extensive evidence on the impact of pharmacist-led medication reviews on early hospital readmission for extreme age populations.

**Trial registration:**

Current Controlled Trials, NCT02734017. Registered on 4 May 2016.

**Electronic supplementary material:**

The online version of this article (doi:10.1186/s13063-017-1798-6) contains supplementary material, which is available to authorized users.

## Background

Early hospital readmission of patients after discharge is a public health problem. One major cause of hospital readmission is dysfunctions in integrated pathways between community and hospital care that can cause adverse drug events (ADE). An ADE is generally defined as a side effect (anticipated or unanticipated) of an administered medication; it may be due to an adverse drug reaction or a medication error [1]. Furthermore, the French ENEIS 2 study showed that 1.3% of hospital stays originated from serious ADE in 2009 [2]. Data from the literature show that older patients and children are at high risk of medication errors specifically at hospital admission and discharge [3–5].

In accordance with the World Health Organization (WHO) ("Assuring medication accuracy at transitions in care”) and French health authorities [6], developing programs on the securing patients’ medications is crucial through the course of care [7]. Indeed, transitions between community and hospital settings are at the highest risk of medication errors [3].

In this context, the pharmacist-led medication review may appear to be a way to improve patient safety. The medication review is a structured, critical examination of a patient’s medicines; the objective is to reach agreement with the patient regarding treatment to optimize the impact of medicines, minimize the number of medication-related problems and reduce waste [8]. When performed by pharmacists, this is called a pharmacist-led medication review.

The pharmacist-led medication review has been demonstrated to be an effective strategy to reduce medication discrepancies at admission and discharge [9, 10]. However, it is difficult to assess the real impact of the pharmacist-led medication review in specific high-risk populations, such as pediatric and geriatric populations.

Meta-analysis shows that pharmacist-led medication reviews have brought substantial reductions in the rate of readmission [10]. This endpoint is important because the pharmacist aims to improve reductions in medication errors as well as the transmission of information to the interfaces of the care system [11]. However, the studies included have certain limitations: (1) a low level of evidence, (2) the heterogeneity of experimental intervention (medication reconciliation associated or not with treatment review or medication service liaison) [12–20], (3) a different delay and different modalities in the endpoint assessment and (4) only one randomized controlled trial (RCT) performed in a pediatric population [12–16].

In such a context, it is important to demonstrate the effectiveness of a pharmacist-led medication review in high-risk populations (geriatrics and pediatrics) using a high level of evidence based on a large randomized controlled clinical trial. In our study, we hypothesized that this pharmacist-led medication review—which consists of (1) preventing medication errors at transitions (admission or discharge) through medication reconciliation, (2) analyzing and revising treatment, (3) informing and educating patients and (4) coordinating health professionals—may decrease hospital readmissions.

The primary objective of this study is to assess the impact of the pharmacist-led medication review on the rate of all-cause hospital readmissions and/or all-cause death at 30 days following initial hospitalization discharge. The secondary objectives are to assess the impact of the pharmacists-led medication review on the rate of all-cause readmission in care units, the rate of emergency department visits, the rate of mortality, the number of consultations post-discharge and patient treatment satisfaction.

## Methods/Design

### Design

This is a prospective, randomized, controlled and open-label study comparing two patient care strategies: (1) the experimental group, receiving a pharmacist-led medication review; (2) the control group, receiving typical care. The open procedure is the only possible option because of the nature of the intervention, which requires that healthcare workers and participants not be blinded. The study protocol was designed using the recommendations of the Consolidated Standard of Reporting Trials (CONSORT) statement. The Standard Protocol Items: Recommendations for Interventional Trials (SPIRIT) checklist (Additional file 1) and figure (see Fig. 1) were used to prepare the study protocol.

**Fig. 1 Fig1:**
[figure not shown]
Template ConcReHosp Study

### Recruitment of participants and study setting

The recruitment will be performed in a pediatric department and a geriatric and internal medicine department. The methodological support will be provided by the Clinical Research Unit (Unité d’Aide Méthodologique à la Recherche Clinique, AP-HM, France). The central pharmacy of AP-HM is in charge of overall coordination of the study and implementation of interventions.

### Inclusion and exclusion criteria

The details of the inclusion and exclusion criteria are provided in Table 2. The main inclusion criteria are (1) a pediatric patient hospitalized in a multidisciplinary pediatric care unit or (2) adult patient over 65 years old hospitalized in a geriatric and internal medicine post-emergency care unit where nearly all patients are admitted after an emergency room stay. The main exclusion criteria are patients whose care requires regularly/programmed re-hospitalization less than 30 days after discharge from the initial hospitalization.

**Table 2 Tab2:** Selection criteria

Inclusion criteria
- Subject aged under 18 or over 65 years
- Subject hospitalized in the multidisciplinary pediatric care unit or internal medicine, therapeutics, post-emergency care unit, regardless of the reason for admission
- Subject with or without any comorbidity
- Living in France
- With national public funded health insurance
Exclusion criteria
- Patients whose care requires regular/programmed re-hospitalization less than 30 days after discharge from initial hospitalization.
- Vulnerable persons according to French law (pregnant women, adults under guardianship, persons deprived of liberty)

Participants will be recruited within 24 h after admission in the care service. When a new patient is eligible according to the selection criteria, a participant information sheet presenting the objectives of the study as well as procedures is provided and explained:To the adult patient or caregiver in the case of demented patients (Mini Mental State < 21);To the parents in the case of minor patients.

To reach the target sample, when a patient is admitted into the service, the physician performing the clinical examination of entry reviews the patient's inclusion criteria and considers whether the patient is eligible for study. He or she then informs the pharmacist of the study.

### Randomization

Computer-generated randomized lists will be drawn up before the beginning of the study using a permuted block design under the responsibility of the clinical research unit (AP-HM). The randomization will be stratified by center. The patients will be randomized to the control group or the experimental group using a computer-generated randomization schedule with a 1:1 allocation ratio. The open-label study is the only option because of the involvement of the patient in the medication reconciliation procedure.

## Experimental and control interventions

Each patient included in the study will be randomized in one of the following two groups (see Fig. 2):

**Fig. 2 Fig2:**
[figure not shown]
ConcReHosp study - flow of the intervention

### Control group

In the control group, the pharmaceutical team is only involved in dispensing drugs, including standard pharmaceutical analysis prescription, during the hospital stay. At admission, the medical staff collects the list of current medications. At discharge, the medical team provides a prescription without intervention by the hospital pharmacy team. A report is sent to the community physician at the end of hospitalization.

### Experimental group

Participants in the experimental group receive a pharmacist-led medication review including the following: (1) a medical and pharmaceutical admission medication reconciliation and treatment review, (2) a medical and pharmaceutical medication reconciliation at discharge and treatment review and (3) medication liaison service.

#### Medical and pharmaceutical admission medication reconciliation and treatment review

Medication reconciliation (MedRec) at admission will be performed by a pharmacist or a pharmacy resident within 24 h after patient admission. On Saturdays and Sundays, admission MedRec will take place the following Monday morning, and for patients admitted on holidays, the MedRec will be performed the day after.

The admission MedRec first involves completion of the medication history, with research into information about patient treatment. Data from several sources should be gathered; previous medical and pharmaceutical records before admission or information from the patient him- or herself and/or the family or caregivers, the community pharmacist and physician should be gathered by phone. First, the pharmacist or a pharmacy resident interviews the patient, and then the interview is conducted with the community pharmacist. If there are insufficient data, the pharmacist should call the general practitioner or the specialist. Based on these data, it is possible to formalize the complete list of medications taken by the patient before hospitalization. Then, the list is compared to the admission prescription. Differences from the admission prescription are discussed between the hospital pharmacist and hospital physician. If these are intentional, the hospital physician is asked to note the reason in the medical record. In the case of medication errors, the hospital physician issues a revised prescription.

A pharmacist-led treatment review is systematically associated with MedRec. It consists of pharmaceutical analysis of the prescription.

#### Medical and pharmaceutical medication reconciliation at discharge and treatment review

The medical and pharmaceutical MedRec at discharge consists of comparing the medication history to the hospital discharge prescription to identify possible discrepancies. Differences between medication history and the hospital discharge prescription are discussed between the hospital pharmacist and hospital physician. The differences may be intentional, and if this is the case, the hospital physician notes the changes in the patient record. In the case of unintentional discrepancies (medication errors), the hospital physician issues a new prescription.

A pharmacist-led treatment review is systematically associated with MedRec. It consists of pharmaceutical analysis of the prescription.

#### Medication Liaison Service

At discharge, the medication liaison service includes the following:A comprehensive medication history contains the list of medications that the patient was taking prior to hospitalization and the list of new medications with comments, making it possible to understand the evolution of the treatment.Counseling: A session with the patient explaining the comprehensive medication history, the main adverse drug reactions, warning signs, biological monitoring, indications and an indication of the importance of drug adherence.A discharge letter faxed to the community pharmacist and general practitioner (community physician). This discharge letter will also present medications prescribed before and after hospitalization. Additional comments allow the community pharmacy and physician to understand the patient's revised treatment.

### Endpoints/Evaluation criteria

#### Primary endpoints

The primary endpoint is the rate of all-cause hospital readmission and/or all-cause death and/or emergency department visits occurring within 30 days after the patient discharge from initial hospitalization.

All-cause hospital readmission is defined as an unscheduled hospital stay in a medical or surgery department or intensive care unit, regardless of the reason for admission or duration of stay.

Death is defined as an occurrence of death between discharge and day 30.

Not considered are inpatient services, post-acute care and rehabilitation (PACR) or nursing homes.

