#### Secondary endpoints

The rate of all-cause hospital readmission, as defined in the primary endpoint, within 30 days after the patient discharge from the initial hospitalization.The rate of all-cause emergency department visits occurring within 30 days after the patient discharge from the initial hospitalization. This is the proportion of emergency department visits.The rate of all-cause mortality occurring within 30 days after the patient discharge from the initial hospitalization. This is the proportion of deaths.The number of consultations scheduled or not within 30 days post-hospitalization will be studied. Consultations are defined as interviews with the attending physician, a specialist physician or a nurse.Patient satisfaction with regards to its drug treatment will be measured using the standardized questionnaire “Satisfaction with Medicines Questionnaire (SatMed-Q®)” [21] validated in French [22]. It includes 17 items related to 6 different aspects: effectiveness, adverse effects, ease of use, patient's general opinion, treatment effect on daily life, quality of monitoring and information provided by health professionals. Answers are expressed on a 5-point Likert scale from "Not at all" to "Yes, a lot." There are six scores and an overall score (0 to 100). The evaluation will be conducted at 30 days post-hospitalization during the telephone follow-up.

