### Statistical considerations

#### Sample size, power and statistical methods

The calculation of the required number of subjects was made from the primary endpoint, i.e., the rate of re-hospitalization and/or death.

Based on the literature, mainly a recent meta-analysis including the RCTs working on a pharmacist-led medication review [11], and data provided by the medical information service, the expected proportion of re-hospitalization and/or death in the standard group is 20% (worst case scenario). To detect a difference of at least 6% between the two groups (i.e., 14% re-hospitalization of the experimental group) given a two-sided significance level of 5% and 80% power, 1300 patients are needed (650 in each group). To prevent 10% dropout, a total of 1400 subjects should be included. The recruitment will be open for 18 months, and we expect to recruit about 75 patients per month.

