#### Data analysis

The major principles of the analysis are reported below. However, a specific protocol of the analysis will be provided a second time before the initialization of the study (validated by the investigator coordinator, the person responsible for the analysis, and the biostatistician). The data will be analyzed using SPSS version 17.0 software. Statistical significance is defined as *p* < 0.05. The methodology is based on the Consolidated Standards of Reporting Trials Statement (CONSORT, http:// www.consort-statement.org/consort-statement/) [23].

The full analysis population (including all subjects who will be randomized and at least evaluated at the baseline) will be used in the primary analysis, and the per protocol population (including all subjects who will be randomized and will not have major protocol deviations) will be used in the secondary analysis to assess the robustness of the results. No interim analysis is planned. Demographic and baseline characteristics will be summarized for the two groups (‘standard’ and ‘experimental’ groups). Missing data will not be replaced.

Primary endpoint. The proportions of readmission and/or death at day 30 will be compared between the two groups (chi^2^ test or Fisher’s exact test). Proportions will be presented with 95% confidence intervals. Logistic regression will be performed to adjust potential confounding factors; variables relevant to the models will be selected based on their clinical interest and/or a threshold *p*-value ≤ 0.1 during univariate analysis. The center will be automatically entered into the model. The final models expressed the odd ratios and their 95% confidence intervals. The unadjusted analysis will be the primary analysis, and the adjusted analysis will be the complementary analysis.

Secondary endpoints. Qualitative variables will be compared between the two groups using the same procedure. The number of consultations and satisfaction scores will be compared between the two groups using Student’s *t* test or Mann-Whitney test. Multivariate approaches (logistic or linear regressions) will be performed using the same procedure.

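### The primary endpoint includes emergency department visits where it is defined but not in the abstract, objective, sample size or primary test, so the same data can give two primary results

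*Protocol article*

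**What the plan says.** The section that formally defines the outcome, Primary endpoints, has three components: "The primary endpoint is the rate of all-cause hospital readmission and/or all-cause death and/or emergency department visits occurring within 30 days".

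Four other places have two components:

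- Abstract, Methods/design: "The primary endpoint will be the rate of readmissions and/or death at 30 days following initial hospitalization discharge".
- Background, primary objective: "the rate of all-cause hospital readmissions and/or all-cause death at 30 days following initial hospitalization discharge".
- The sample size section, opening sentence: "The calculation of the required number of subjects was made from the primary endpoint, i.e., the rate of re-hospitalization and/or death".
- Data analysis, primary endpoint: "The proportions of readmission and/or death at day 30 will be compared between the two groups".

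The aim stated in the Background part of the abstract also leaves emergency department visits out. The Secondary endpoints section lists them as an outcome in their own right: "The rate of all-cause emergency department visits occurring within 30 days after the patient discharge from the initial hospitalization". Table 3 collects them on a separate line.

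**The concern.** A confirmatory trial needs one primary endpoint, and this document states two. Allocation is open-label. Outcomes are collected by a telephone call at 30 days, and the care unit is contacted only when a hospitalization or emergency visit is reported. In that setting, an unresolved definition would allow either composite to be presented as the primary result once the group comparison is known.

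The design calculation is also affected. The 20% and 14% proportions are given for re-hospitalization and/or death only. If the three-part definition governs, the stated 80% power refers to a different outcome from the one being tested.

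**Working it through.** **Step 1: can the two versions mean the same thing?** They could if an emergency department visit counted as a readmission. The Primary endpoints section rules this out: "All-cause hospital readmission is defined as an unscheduled hospital stay in a medical or surgery department or intensive care unit". A patient seen in the emergency department and sent home does not meet that definition.

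| Patient's 30-day course | Three-part definition (Primary endpoints) | Two-part definition (abstract, objective, sample size, analysis) |
|---|---|---|
| Unscheduled medical, surgical or intensive care stay | event | event |
| Death | event | event |
| Emergency department visit only | event | non-event |
| None of these | non-event | non-event |

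The third row is where the two primary results diverge. The separate secondary listing does not settle the matter, because readmission and death are also listed separately as secondary endpoints. The contradiction rests on the objective, sample size and analysis text.

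**Step 2: which endpoint does the sample size belong to?** Inputs from the sample size section: control 20%, experimental 14%, two-sided 5%, 80% power, 650 per group. Allocation is 1:1 (Randomization).

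With d = p1 − p2, p̄ = (p1 + p2)/2, A = √[2p̄(1 − p̄)] and B = √[p1(1 − p1) + p2(1 − p2)]:

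- n per group = (1.960·A + 0.842·B)² / d². With p̄ = 0.17, A = 0.5312, B = 0.5295 and d = 0.06, n = 614.1, so 615.
- Continuity-corrected n = (n/4)·[1 + √(1 + 4/(n·d))]² = 647 per group, or 1294 in total.

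The corrected figure agrees with the stated 650 per group (1300 in total). The sample size is therefore sound for the two-part endpoint.

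Power at 650 per group = Φ[(d·√650 − 1.960·A)/B] = Φ(0.923) = 82.2%, or 80.2% with continuity correction.

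**Step 3: what power would the three-part endpoint have?** The document gives no proportion for it. The control proportions below are assumptions for illustration. Values are for 650 per group, without continuity correction.

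| Assumed control proportion | 6-point difference kept: power | n per group for 80% | 30% relative reduction kept: power | n per group for 80% |
|---|---|---|---|---|
| 20% (as planned) | 82.2% | 615 | 82.2% | 615 |
| 25% | 74.3% | 748 | 91.2% | 466 |
| 30% | 68.4% | 859 | 96.2% | 367 |
| 35% | 64.0% | 948 | 98.6% | 297 |
| 40% | 61.1% | 1016 | 99.6% | 244 |

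The 30% relative reduction is 6/20 from the plan's own figures. With continuity correction, the 6-point results at 25% and 30% are 72.1% and 66.1%. Power can therefore move in either direction, and nothing in the document says which case applies.

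**The case against.** The best defence is that the mention of emergency department visits is a stray insertion. The only primary test described is on readmission and/or death. The sample size section equates the primary endpoint with that pair. Within the Primary endpoints section, readmission and death receive definitions and emergency department visits do not. A separate analysis protocol, validated before the study starts, is also promised and may settle the point.

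Much of this is fair, and it makes the two-part version the more likely intention. It does not remove the conflict. The three-part wording stands in the section a reader would consult for the definition, and no other text overrides it. The choice of primary endpoint is not a detail the article leaves open for later: it is stated, in two incompatible ways.

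A second objection is that a power loss is speculative. That stands. The control proportions above 20% are assumed, and a constant relative reduction would raise power. The supportable statement is that power for the three-part endpoint is undefined.

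It might also be said that 20% was already labelled a worst case. That label gives no protection if the difference is fixed at 6 points, because power then falls as the control proportion rises from 20% towards 50%. This is true of either composite, so it adds little to the present point.

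**Conclusion.** The contradiction is real and must be corrected. It follows from the text alone and needs no assumption: the formal definition counts an emergency-department-only patient as an event, and the abstract, objective, sample size and primary test do not.

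The sample size arithmetic is not at fault. It reproduces for 20% versus 14% and belongs to the two-part endpoint. For the three-part endpoint the stated 80% power has no basis. Over assumed control proportions of 25% to 40% it ranges from about 61% (6-point difference kept) to over 99% (30% relative reduction kept). The more serious consequence is that an open-label trial is left with a choice of primary result.

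**What to change.** In the Primary endpoints section, remove emergency department visits from the composite, so that the primary endpoint is unscheduled all-cause readmission and/or all-cause death within 30 days of discharge. This matches the objective, the sample size and the primary test. Emergency department visits stay as the existing secondary endpoint. If the three-part composite is of interest, name it as a secondary endpoint.

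If the sponsor in fact intends three parts, the abstract, the objective and the analysis text must be changed to match. The control proportion, target difference and power must then be restated for that composite.

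The first route costs one sentence and needs no extra patients or data. The second changes several sections and may change the sample size. The Trials status section reports that recruitment was already open, so either change should be made as a dated amendment before anyone has compared outcomes between the groups.
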